***ICD-10* code and description of diagnosis**
S71.87: grade-I soft tissue damage due to open fracture or dislocation of hip and thighS71.88: grade-II soft tissue damage due to open fracture or dislocation of hip and thighS71.89: grade-III soft tissue damage due to open fracture or dislocation of hip and thighS81.87: grade-I soft tissue damage due to open fracture or dislocation of lower legS81.88: grade-II soft tissue damage due to open fracture or dislocation of lower legS91.88: grade-II soft tissue injury due to open fracture or dislocation of footS78: traumatic amputation of hip and thighS88: traumatic amputation of lower legS98: traumatic amputation of upper ankle and footT84.6: infection and inflammatory reaction due to internal osteosynthesis device (any location)T84.7: infection and inflammatory reaction from other orthopedic endoprostheses, implants, or grafts

Inclusion and exclusion criteria.

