### Data Sampling

#### Clinical and Health Economic Evaluation

Studies show that, in approximately 40% of cases, complications occur during the treatment in open fractures [40]. The new form of care is realistically intended to reduce the complication rate to 30%. A type-1 error (α) of 5%, a type-2 error (β) of 20% (80% power), and an intraclass correlation coefficient of ρ=0.05 are assumed [36]. Considering the transition phase and a dropout rate of 20%, the total number of cases required to demonstrate a treatment effect is 3366 patients (of whom n=1377, 40.91% would be in the control phase; n=1428, 42.42% would be in the intervention phase; and n=561, 16.67% would be in the transition phase). This equates to 17 patients per hospital per 3-month interval.

Only patients who can give consent and who have statutory health insurance will be included in the project and will give their written consent to participate and share their data in the use of telemedicine. The study will include patients with fractures of the extremities with open soft tissue damage (according to Gustilo et al [41]) or with postoperative complications (according to the criteria of the Association of the Study of Internal Fixation Anti-Infection Task Force) or people with unplanned resurgery within 6 months of initial surgery. Specifically, these are *International Statistical Classification of Diseases and Related Health Problems, 10th Revision* (*ICD-10*), diagnoses [42] related to open soft tissue damage in fractures or dislocations, amputations of the lower extremity, infections of joints or joint endoprostheses of the lower extremities [43], and pseudarthrosis and delayed fracture healing of the lower extremity (see the list in Textbox 1).

Patients who are not capable of giving consent, who do not give their consent to participate or to data transfer, or who do not have statutory health insurance will be excluded from the study. Also excluded will be persons to whom the aforementioned *ICD-10* diagnoses do not apply (ie, who do not have a fracture of the extremities or extremities or have a closed fracture of the extremities without open soft tissue damage and who do not experience a postoperative complication within 6 months of initial surgery). The inclusion and exclusion criteria are summarized in Textbox 2.

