*International Statistical Classification of Diseases and Related Health Problems, 10th Revision* (*ICD-10*), diagnoses to be included in the EXPERT (Extremity boards for process optimization, evaluation, risk minimization, and therapy optimization for fractures with soft tissue damage or postoperative infection of the lower extremities in the trauma network) study.

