**Clinical criteria**
Inclusion criteriaPatients who meet at least one of the following 2 criteria: fractures of the extremities with open soft tissue damage (according to Gustilo et al [41]) OR postoperative complications (according to the criteria of the Association of the Study of Internal Fixation Anti-Infection Task Force) or unplanned reoperation within 6 months of initial surgery; these criteria are operationalized via the *International Statistical Classification of Diseases and Related Health Problems, 10th Revision*, codes for the following: open soft tissue damage in fractures or dislocations as well as amputations of the lower extremities; infections of the lower extremities (excluding joints and joint arthroplasty); infections of joints or joint endoprostheses of the lower extremities; pseudarthrosis and delayed fracture healing of the lower extremitiesExclusion criteriaPatients who meet both of the following criteria: no fracture of the extremities or closed fracture of the extremities without open soft tissue damage AND no postoperative complication or unplanned reoperation within 6 months of initial surgery

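### The ICD-10 list in Textbox 1 does not match the inclusion criteria it is meant to apply: three open-fracture grade entries and all pseudarthrosis or delayed-healing codes are absent

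*Protocol article*

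**What the plan says.** Four places in the protocol article define who is eligible.

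- **Data Sampling, Clinical and Health Economic Evaluation.** The criterion is clinical and carries no grade limit: "The study will include patients with fractures of the extremities with open soft tissue damage". Postoperative complications and unplanned reoperation within 6 months of the first operation are the other routes in. The paragraph then names diagnosis groups, ending with "pseudarthrosis and delayed fracture healing of the lower extremity (see the list in Textbox 1".
- **The same section, on exclusions.** "Also excluded will be persons to whom the aforementioned *ICD-10* diagnoses do not apply". A gloss follows, which describes these persons as having no fracture or only a closed one, and no postoperative complication.
- **Textbox 2, clinical criteria.** The same ungraded criterion is repeated, and the link to codes is explicit: "these criteria are operationalized via the" ICD-10 codes for the named groups. The exclusion criteria there are worded clinically and mention no grade.
- **Textbox 1.** Its title presents it as the list of "diagnoses to be included in the EXPERT" study. The lower-leg entries stop at grade II and the next entry is a foot code: "grade-II soft tissue damage due to open fracture or dislocation of lower legS91.88" (the entries run together in the text).

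**The concern.** When a protocol states a clinical criterion and also says that the criterion is applied through a code list, the two must pick out the same patients. Here they do not. Staff who enroll by code find no soft-tissue entry for a grade III open fracture of the lower leg, while staff who enroll by the clinical wording take the patient. Both can claim to follow the protocol.

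With 31 hospitals enrolling, the severity mix could differ between sites for reasons unrelated to their patients. The missing lower-leg entry also touches the injury on which the Introduction builds its case: it argues from the cost of open lower-leg fractures and from UK standards for severe ones. If these patients are under-represented, a conclusion about open fractures of the lower extremity would describe a population that was not fully enrolled. The planning rate of 40% complications, stated for open fractures without a grade limit, would then have to be justified for a different group.

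**Working it through.** No sample-size or error-rate figure underlies this point, so the check compares the list with the criteria.

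**Step 1. Contents of Textbox 1.** It has 11 entries: 6 for open soft tissue damage, 3 for traumatic amputation (S78, S88, S98) and 2 for implant-related infection (T84.6, T84.7); 6 + 3 + 2 = 11.

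**Step 2. The soft-tissue entries by region and grade.**

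| Region | Grade I | Grade II | Grade III | Listed |
|---|---|---|---|---|
| Hip and thigh | S71.87 | S71.88 | S71.89 | 3 of 3 |
| Lower leg | S81.87 | S81.88 | absent | 2 of 3 |
| Foot | absent | S91.88 | absent | 1 of 3 |

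Listed: 3 + 2 + 1 = 6 of 9. Absent: 9 − 6 = 3. By the list's own numbering pattern these would be S81.89, S91.87 and S91.89; that is an inference from the pattern.

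**Step 3. The named diagnosis groups.** The text sends the reader to Textbox 1 for pseudarthrosis and delayed fracture healing. None of the 11 entries is for either condition.

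**Step 4. One patient under each rule.** Take a grade III open lower-leg fracture with no amputation and no implant infection.

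- Clinical criterion (Data Sampling; Textbox 2): eligible.
- Clinical wording of the exclusion (the gloss in Data Sampling; Textbox 2): not excluded, because the fracture is open.
- Code list (Textbox 1): no soft-tissue entry, and neither the amputation nor the infection codes apply.

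Grade I and grade III open fractures of the foot give the same conflict.

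**Step 5. Is a deliberate restriction visible?** Grade III is kept for the thigh and traumatic amputations are listed at all levels, so severity is not the filter. Grade II alone for the foot follows no rationale in the article. No section gives a reason for any of the omissions.

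**Step 6. Can the effect on the planned rates be computed?** No. That would need the share of patients in the missing cells and their complication risk. The article gives neither, and the trial also enrolls patients with postoperative complications, so even a share among open fractures would not carry over to the whole sample. The missing cells do not all point one way either: two are grade III and one is grade I.

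**The case against.** The strongest reply is that no patient is actually excluded. The exclusion sentence is explained by its own gloss, which covers only people with no fracture or a closed fracture and no complication. Textbox 2 words its exclusions clinically. The diagnoses referred to in the exclusion sentence may be the ungraded groups named just before it. This stands as far as it goes: a reader might infer that grade III lower-leg fractures are barred from the trial, and the documents do not support that. What remains is that Textbox 2 says the criteria are applied through codes, and the list of codes lacks these patients.

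A second reply is that the list is simply incomplete as printed. The absence of pseudarthrosis and delayed-healing codes supports this, and S81.89 and S91.87 would have been adjacent lines. A line lost in converting the textbox to text cannot be wholly ruled out, although the entries run on without a visible gap. This too largely stands, and it is why the point is an inconsistency to be reconciled and not a criticism of a design choice.

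Third, the consequences are bounded. Some severe lower-leg injuries still enter through S88, T84.6 or T84.7. Trained staff enroll the patients; nothing in the article has insurers selecting them. No section shows that hospitals do in fact differ in how they select. Each hospital contributes both control and intervention periods, so a stable difference in case mix between hospitals would be largely shared by both phases. It would bear more on generalizability than on the treatment contrast.

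**Conclusion.** The inconsistency is real and can be read directly from the article: 3 of 9 region-by-grade entries are absent, and no code is given for two diagnosis groups that the text says are in the list. Eligibility is therefore stated in two ways that disagree for identifiable patients, chiefly those with grade III open lower-leg fractures without amputation or a listed implant infection. Enrollment may then differ in severity between hospitals, and the population studied may differ from the one described.

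This rests on Textbox 1 as it appears in the article being the list that sites use. If sites hold a complete list, only the publication needs correcting.

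Two stronger readings should not be drawn. One is that the trial was designed to leave out severe lower-leg fractures; the retained thigh grade III and amputation codes, and the other gaps in the list, speak against it. The other is that power falls by a stated amount; any such figure would rest wholly on assumed grade shares and risks.

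**What to change.** Reconcile Textbox 1 with Data Sampling and Textbox 2. Add the missing entries (grade III for the lower leg, grades I and III for the foot, and the pseudarthrosis and delayed-healing diagnoses), and say whether the clinical wording or the code list governs when they disagree. Notify sites prospectively.

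If any omission is intended, state it as an exclusion in Textbox 2, recheck that the 40% planning rate fits the restricted population, and limit the conclusion accordingly.

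Patients missed earlier should not be enrolled retrospectively. Consent is required before entry (Ethical Considerations), and quality of life is measured at enrollment (Outcomes and Measures).

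The cost is a corrected list and a notice to 31 hospitals. One caution applies: in a stepped-wedge trial, a change in how eligibility is applied during recruitment falls unevenly on the control and intervention phases. The date of the notice and each patient's fracture grade should therefore be recorded, so that the analysis can take account of any shift in case mix.

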**Formal criteria**
Inclusion criteriaConsent to study participation and data transferLegal capacity to consent to study participationStatutory health insuranceExclusion criteriaLack of consent to study participation and data transferUnclear legal capacity or capacity to consentNot covered by statutory health insurance
**Clinical criteria**
Inclusion criteriaPatients who meet at least one of the following 2 criteria: fractures of the extremities with open soft tissue damage (according to Gustilo et al [41]) OR postoperative complications (according to the criteria of the Association of the Study of Internal Fixation Anti-Infection Task Force) or unplanned reoperation within 6 months of initial surgery; these criteria are operationalized via the *International Statistical Classification of Diseases and Related Health Problems, 10th Revision*, codes for the following: open soft tissue damage in fractures or dislocations as well as amputations of the lower extremities; infections of the lower extremities (excluding joints and joint arthroplasty); infections of joints or joint endoprostheses of the lower extremities; pseudarthrosis and delayed fracture healing of the lower extremitiesExclusion criteriaPatients who meet both of the following criteria: no fracture of the extremities or closed fracture of the extremities without open soft tissue damage AND no postoperative complication or unplanned reoperation within 6 months of initial surgery

#### Work-Related Evaluation

Physicians and nurses who are or will be involved with the project take part in the work-related evaluation. With medium to small effect sizes (η^2^>0.05 and <0.15), a type-1 error (α) of 5%, and a type-2 error (β) of 20% (80% power), a minimum number of 120 people per measurement point is required for the work- and project-related evaluation (60 people each in the control and treatment groups). A total of 4 employees per clinic at measurement time t0 and 4 employees at measurement time t1 are included in the sample. This results in 31 × 8 = 248 elevations. Care is taken to interview physicians and nurses in equal parts, all of whom are or will be involved in the project measures.

Regarding the interviews for the assessment of the objectives and project implementation, 2 persons from the nursing service and 2 persons from the medical profession are to be interviewed at time t1 in the clinics that are already implementing the new form of care. Approximately 72 people from at least 18 clinics will take part in the interviews.

### Ethical Considerations

Ethics approval has been granted by the ethics committee of the Medical Association of Westphalia-Lippe under the number 2023-067-f-S. This study is conducted per the tenets of the Declaration of Helsinki. All data have been collected, anonymized, analyzed, and stored in accordance with German General Data Protection Regulation legislation based on the European General Data Protection Regulation. The accordance to these data protection standards is approved and enforced by OFFIS-Institute for Information Technology, an institute related to the University of Oldenburg specializing on research services and data protection.

Participation is voluntary, and participants are required to provide oral and written consent to take part before entering the study. All participants received oral and written information before signing a consent form upon enrollment in the trial, and no financial compensation was made to participants in the study. The protocol was registered with the German Clinical Trials Register database (DRKS00031308).

### Outcomes and Measures

#### Clinical and Health Economic Evaluation

The primary outcome and various secondary clinical outcomes are recorded based on data from the clinical case file as well as routine data from the health insurance companies.

The primary clinical outcome is the complication rate of open fractures or the occurrence of postoperative complications, which is collectively defined as a dichotomous outcome. Either the occurrence or nonoccurrence of complications is observed. The following events are complications if they occur within 6 months of enrollment in the sample: (1) occurrence of pseudarthrosis (incomplete fracture healing; *ICD-10* code M96.0); (2) occurrence of chronic osteomyelitis (*ICD-10* code M86.69); (3) unplanned follow-up procedures, such as wound revisions and Negative Pressure Wound Therapy (*ICD-10* code S81.801); (4) deviation from standardized antibiotic therapy (extension of the duration of therapy or change or expansion of the active substance; *ICD-10* code T36.95); (5) occurrence of antibiotic-associated complications (eg, clostridia infection or allergy; *ICD-10* code B96.7); (6) infection with resistant germs (eg, methicillin-resistant *Staphylococcus aureus*) that occurred during inpatient treatment and did not exist at the time of trauma (*ICD-10* code A49.02); (7) need for unplanned inpatient treatment; and (8) death of the patient related to the trauma (not due to other causes).

Secondary clinical outcomes include the number of antibiotics administered, limb function, and health-related quality of life (HRQoL) [44,45].

Health economic outcomes are mapped through claims data from health insurance companies. These will be recorded for each patient included in the project up to 6 months after enrollment in the sample. Specifically, the following features will be recorded: (1) use of health services (eg, contact with physicians and therapists, operations, and inpatient stays), (2) cost of health care services (inpatient hospital costs, outpatient costs, rehabilitation costs, medical and medical aid costs, drug costs, and total costs), (3) number of days on which there is incapacity for work, and (4) number of days on which sickness benefits are received.

Table 1 provides an overview of the clinical and health economic outcomes used in this study.

Patients’ HRQoL is assessed at the time of enrollment and 6 months later using two internationally used measuring instruments: (1) the German-language version of the royalty-free Veterans RAND 36-item Health Survey [44] and (2) the German-language version of the EQ-5D of the EuroQol Group [45,46].

The Veterans RAND 36-item Health Survey is a generic profile questionnaire and measures HRQoL regarding the dimensions “Physical Functioning,” “Role-Physical,” “Role-Emotional,” “General Health,” “Social Functioning,” “Vitality,” “Bodily Pain,” and “Mental Health.”

The EQ-5D as a generic index instrument contains the 5 dimensions “Mobility,” “Self-care,” “Usual activities,” “Pain/Discomfort,” and “Anxiety/depression” as well as a visual analog scale. The results of the EQ-5D can be used to create a health profile as well as calculate an index value [46]. As an instrument validated in Germany, the index for HRQoL recorded using the EQ-5D is particularly well suited as a health economic outcome measure [46].

**Table 1 table1:** Clinical and health economic outcomes.

Outcome					Data source			Measurement time

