**Primary outcome**								
	**Complication rate, defined as the occurrence of at least 1 of the following events within 6 months of trauma [42]:**			Clinical and claims data			6 months	
		Occurrence of pseudarthrosis (incomplete fracture healing)	Clinical data			6 months		
		Occurrence of chronic osteomyelitis	Clinical data			6 months		
		Unplanned follow-up procedures, such as wound revisions and NPWT^a^	Clinical and claims data			6 months		
		Deviation from standardized antibiotic therapy (extension of the duration of therapy or change or expansion of the active substance)	Clinical and claims data			6 months		
		Occurrence of antibiotic-associated complications (eg, clostridia infection or allergy)	Clinical and claims data			6 months		
		Infection with resistant germs (eg, MRSA^b^) that occurred during inpatient treatment and did not exist at the time of trauma [43]	Clinical data			6 months		
		Need for unplanned inpatient treatment	Clinical and claims data			6 months		
		Death of the patient related to the trauma (not due to other causes)	Clinical and claims data			6 months		

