### Strengths and Limitations

When measuring the quality of treatment in trauma surgery, several influencing factors must be considered. The type of injury, the extent of anatomical reconstruction during surgery, soft tissue management, perioperative management, and rehabilitation protocols as well as patient compliance have a major influence on the outcome and make evaluation difficult. For our study, we chose 4 outcome measures: the complication rate after initial surgery (nonunion, infection, unplanned surgical revision, and need for prolonged antibiotic therapy), the number of applied antibiotics, the functionality of the injured limb, and HRQoL.

The clinical outcome is examined using a stepped-wedge design, which allows for the statistical consideration of time effects. The design also has practical advantages, such as the easy implementation of a staggered rollout. Among the weaknesses of a stepped-wedge design are time-sensitive recruitment efforts, complex randomization requirements when assigning hospitals to different cohorts or wedges, the assumption of high treatment schedule fidelity, and effects of the observation (the so-called Hawthorne effect) [74].

We choose a difference-in-difference design, a widely used quasi-experimental design in clinical research, to evaluate work-related outcomes. This design eliminates confounding by comparing outcomes before and after treatment. However, the design relies on a parallel-slopes assumption, which is hard to manage and may not always apply [75].

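### The ICD-10 code attached to unplanned follow-up procedures (S81.801) belongs to a lower-leg diagnosis category, so it cannot identify a procedure and does not fit the other eligible sites

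*Protocol article*

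**What the plan says.** In Outcomes and Measures (Clinical and Health Economic Evaluation), the primary outcome is dichotomous: a patient has an event if any one of eight listed complications occurs within 6 months of enrolment. The third reads "unplanned follow-up procedures, such as wound revisions and Negative Pressure Wound Therapy", followed in parentheses by the ICD-10 code S81.801. No other code is given for it. The same section says the outcomes are recorded from "data from the clinical case file as well as routine data from the health insurance companies".

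Table 1 repeats the item as "Unplanned follow-up procedures, such as wound revisions and NPWT", without a code, and names both clinical and claims data as its source.

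Under Data Sampling, eligibility is described through ICD-10 "diagnoses [42] related to open soft tissue damage in fractures or dislocations" and related conditions. Textbox 1 lists the entry codes, and Textbox 2 says that the clinical entry criteria are put into operation through ICD-10 codes.

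Among the claims content collected for the health economic outcomes, the article lists "contact with physicians and therapists, operations, and inpatient stays".

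**The concern.** The event is a procedure; the code comes from a classification that the article uses for diagnoses, and from a category that the article uses for one body region. The two do not match, and the mismatch can be seen from the article alone.

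This is a stated rule that does not fit its event, which is different from a detail left to a fuller document. For claims extraction it is also the only rule that the article supplies for this event. An analyst who applied it could count a lower-leg diagnosis with no procedure behind it, and would miss procedures at other sites. Because one positive item makes the whole composite positive, an error in this item passes straight into the primary outcome unless another item or source corrects it. The item is not incidental: Strengths and Limitations summarises the complication rate as "nonunion, infection, unplanned surgical revision, and need for prolonged antibiotic therapy", and a lower reoperation rate is among the clinical hypotheses.

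**Working it through.** The article states no figure for this event, so there is nothing to reproduce. The check sets the outcome code beside the article's own list of entry codes.

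**Step 1: does the code describe a procedure?** Data Sampling and Textbox 1 present ICD-10 as a list of diagnoses. A diagnosis says what the patient has. It does not say that an operation took place, when it took place, or whether it was planned. The event definition needs all three.

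**Step 2: does the code fit every eligible site?**

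| Entry codes in Textbox 1 | Site given there | In category S81? |
|---|---|---|
| S81.87, S81.88 | lower leg | yes |
| S88 | lower leg (amputation) | no, but same region |
| S71.87, S71.88, S71.89, S78 | hip and thigh | no |
| S91.88, S98 | foot (S98 also upper ankle) | no |
| T84.6 | any location | no |
| T84.7 | no site named | no |

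A lower-leg category does not describe a revision at the hip, thigh or foot, and there is no reason to expect it for an implant infection elsewhere. Capture by this code would therefore differ by injury site.

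**Step 3: is the code the only route to the event?** No. Table 1 also takes the item from clinical data. The seventh item, unplanned admission, has no code, is taken from clinical and claims data, and is not limited to a site. A revision that needed such an admission would make the composite positive through that item.

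**Step 4: can the effect be sized?** The planning rates are 40% ("in approximately 40% of cases, complications occur during the treatment in open fractures") and 30%. If only a share *s* of composite events were captured, equally in both phases, the rates would be 0.40*s* and 0.30*s*. The difference would be 0.10*s*, smaller than the planned 10 percentage points, and the ratio would stay at 0.30/0.40 = 0.75. This gives a direction only: missed events shrink the absolute contrast and cost power. The article gives no rate for this item, no split of patients by site and no overlap between items, so *s* is unknown and no value is proposed.

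**The case against.** The strongest reply is that the code is a label and not the operational definition. The event is defined in words, the code stands in parentheses, Table 1 omits it, and the seventh and eighth items carry no code, so detection cannot rest on codes throughout. This stands as a limit on the harm. It does not make the code right, and the article does not say which source decides when claims and case file differ.

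Four stronger readings are tempting, and the document does not support them:

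- *Procedures outside the lower leg are lost.* This does not follow, because the case file and the unplanned-admission item remain as routes of capture.
- *Repeat coding of the entry injury would be counted as an event.* The entry codes are S81.87 and S81.88; the outcome code is S81.801. Repeating the entry code would produce a false event only if extraction used the three-character category, which is not stated. The article also gives no label for S81.801, so only the meaning of the category is used here.
- *Most patients are affected, because six of the nine S-codes lie outside the lower leg.* That counts codes, not patients, and leaves out those entering under T84.6 and T84.7.
- *This is a main component of the outcome.* The article names it in its summary but gives no rate, so its weight cannot be shown.

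**Conclusion.** The point holds in limited form. S81.801 does not fit the event to which it is attached, by the article's own use of ICD-10 and of category S81. Claims-based capture of unplanned follow-up procedures by that code would be misclassified in a way that depends on injury site.

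The size is unknown. The harm is conditional on the code actually being used for extraction, and it is reduced to the extent that the case file and unplanned admissions recover the events. If events were missed equally in both phases, the result would be a smaller absolute difference and lower power, with the ratio unchanged. No bias between phases has been shown. The point should be corrected because it concerns the primary outcome and costs little, preferably before claims data are extracted.

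**What to change.** 1. Remove S81.801 from the definition of the third event.
2. Identify the event from operation and procedure records in claims and in the case file, at any eligible site.
3. Count procedures within 6 months of enrolment, as the outcome text does. Counting from the first surgery would be unclear for patients who qualify through a complication or reoperation after it. The Table 1 heading counts from trauma and should be brought into line.
4. Use the case file to judge whether a procedure was unplanned, since a dated operation record does not show this either.
5. State which source decides when claims and case file disagree.

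The cost is a change of wording and an extraction specification. Operations are already listed among the claims content and the case file is already collected, so no new data are needed.
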